#### The ACCESS intervention (intervention group)

Participants randomized to the intervention group receive six real-time, one-on-one 60–minute videoconference sessions with the same PA counsellor over a 12-week period. See Table 2 for an overview of the session topics.

**Table 2 pone.0273045.t002:** ACCESS intervention session topics and activities/worksheets.

Sessions	Topics	BCT groupings*	Activities/worksheets
1	Introduction and discovery Welcome and introductions Discuss the benefits of PA and risks of inactivity Discuss goal setting for PA and action planning Discuss PA self-monitoring techniques	Shaping knowledge Natural consequences Goals and planning Feedback and monitoring	1.1 Current PA behaviors 1.2 PA guidelines 1.3 SMART goals 1.4 Action plan #1 1.5 Self-monitoring strategies
2	Setting up for success Discuss what is and is not PA Discuss PA barrier identification and management Update action plan	Shaping knowledge Comparison of outcomes Antecedents Goals and planning	2.1 Pros and cons worksheet 2.2 Stages of change model 2.3 Exploring different types of PA 2.4 Barrier identification 2.5 Barrier management 2.6 Action plan #2
3	Getting going Discuss social support for PA Discuss time management Update action plan	Shaping knowledge Social support Natural consequences Goals and planning	3.1 Types of social support 3.2 Identifying sources of support 3.3 Understanding time management 3.4 Action plan #3
4	Adjusting your perspective Discuss how PA is related to mood Discuss environmental restructuring Update action plan	Shaping knowledge Regulation Comparison of outcomes Feedback and monitoring Antecedents Goals and planning	4.1 Progress Review Worksheet 4.2 Increasing enjoyment 4.3 Journaling your feelings 4.4 Environmental restructuring 4.5 Action Plan #4
5	Reinforcing new behaviors Encourage identifying self as a PA role model Discuss framing/reframing PA Update action plan	Shaping knowledge Self-beliefs Goals and planning	5.1 Progress review and problem solving 5.2 Examining the new you 5.3 Reframing self-talk 5.4 Action plan #5 *Materials from previous sessions* 2.2 Stages of change 3.3 Big picture
6	Keep going Review topics covered throughout the program Explore how PA fits into life long-term Revise or create a new action plan for the next step in PA journey Discuss strategies for managing stress Re-iterate that PA journey is not linear	Shaping knowledge Regulation Goals and planning	6.1 Stress management information sheet 6.2 Progress report 6.3 Long-term action plan

*Notes*. PA = physical activity, referring to all movement including during leisure time, for transport, and as part of one’s work. BCT = behavior change technique.

*BCT groupings refer to the hierarchically-clustered 93 techniques presented in the BCT taxonomy (v1) [47].

The ACCESS intervention is multicomponent and includes essential elements derived from previous studies with young adults who have completed cancer treatment [18], as well as from published interventions yielding significant changes in PA [48]. The intervention targets SDT constructs, focusing specifically on: (1) providing autonomy support, structure, and interpersonal involvement; (2) increasing perceptions of autonomy (i.e., perceived control over one’s actions by providing a rationale, structure, and emphasising responsibility), competence (i.e., perceived mastery of tasks and skills by providing support and encouragement, information feedback, and support barrier identification), and relatedness (i.e., perceived belonging and connection to others by encouraging social support seeking); and (3) increasing autonomous motivation (i.e., acting through self-endorsement and volition because the activity holds inherent interest and/or personal value). Accordingly, the intervention includes several content and relational techniques to augment these SDT constructs and facilitate PA behavior change. Techniques were selected based on the theoretical construct they are proposed to target, wherein we drew on published literature [10, 22, 23, 49] to draw out which techniques target specific SDT constructs. BCTs used to guide the content of the intervention and inform the development of activities/information sheets are presented in Table 2. Moreover, PA counsellors use MBCT and motivational interviewing (MI) techniques that align with SDT [22] for the relational component of the intervention to support the delivery of the content; these are presented in Table 3. As content and relational techniques are interrelated, there is overlap between some techniques presented in Tables 2 and 3. By using MI techniques, PA counsellors aim to help participants explore and resolve their ambivalence toward PA behavior change, and thus they tailor the content of the intervention to match participants’ readiness to change, perceived advantages/disadvantages for change, and self-efficacy beliefs [50]. To this end, PA counsellors avoid argumentation and “roll with resistance,” acting as an engaged problem-solving partner [51]. MI principles and techniques used by PA counsellors, which align with SDT [49], include empathic/reflective listening, asking open-ended questions, prompting participants to ask questions, prompting participants to offer solutions, seeking participants’ permission to provide information and advice, shifting focus, supporting change/persistence, and showing unconditional regard.

**Table 3 pone.0273045.t003:** Overview of ACCESS intervention components organized by primary SDT construct.

Primary psychological need targeted	Relational techniques	Descriptions
Autonomy	Provide choice (MI/MBCT)	PA counsellor offers choices and options
	Acknowledge participants’ perspectives on behavior (MI/MBCT)	PA counsellor takes time to understand participants’ perspectives on PA and recognize their challenges and efforts. PA counsellor encourages participants to explore and share their perspectives on the causes and perpetuating factors of their current PA behavior
	Provide a meaningful rationale (MBCT)	PA counsellor provides a meaningful rationale for undertaking PA
	Use of non-controlling, informational language (MBCT)	PA counsellor uses informational, non-judgmental language that conveys freedom of choice, collaboration, and possibility when communicating with participants
	Intrinsic goal orientation (MBCT)	PA counsellor encourages identification of intrinsic goals
	Explore life aspirations and values (MBCT)	PA counsellor has participants identify and list important life aspirations, values and/or long-term interests, and has them explore how changes in PA could be linked to them
	Provide structure (MI)	PA counsellor sets parameters within which choice and agency can take place and provides support to initiate action
	Encourage self-experimentation and self-initiation of behavior (MBCT)	PA counsellor prompts participants to experiment and self-initiate PA that could be fun and enjoyable, experienced as a positive challenge, seen as an opportunity for learning or personal expression, and/or associated with skill development
	Emphasize responsibility (MI)	PA counsellor encourages participants to take on responsibility in decision making and/or leadership
	Prompt identification of sources of pressure for behavior change (MBCT)	PA counsellor helps participants identify possible sources of pressures and expectations
	Explore reasons (MI)	PA counsellor explores participants’ reasons for changing their PA behavior
Competence	Offer constructive, clear, and relevant feedback (MBCT)	PA counsellor provides specific relevant, tailored, non-evaluative feedback on participants’ PA goal progress and behavior
	Provide informational feedback (MI)	PA counsellor provides feedback offering information of *how* participants achieved/did not achieve a desired outcome, rather than generic praise/criticism
	Barrier identification (MI)	PA counsellor works with participants to identify barriers to PA behavior change and identify ways of overcoming them
	Assist in setting optimal challenge (MBCT)	PA counsellor assists participants in identifying goals that are realistic, meaningful, challenging, and achievable
	Help develop a clear and concrete plan of action (MBCT)	PA counsellor and participants develop an action plan to work toward a PA behavior goal
	Clarify expectations (MBCT)	PA counsellor has participants discuss their expectations in terms of PA behavior change (i.e., has them identify goal(s)), both its experiential elements (process) and outcomes
	Promote self-monitoring (MBCT)	PA counsellor promotes monitoring of progress, and discusses options for monitoring tools/means and metrics for success
	Address obstacles for change (MBCT)	PA counsellor helps participants identify likely barriers to PA behavior change, and explore how to overcome them
	Explore ways of dealing with pressure (MBCT)	PA counsellor discusses ways to manage and limit effects of pressuring contingencies that would undermine perceptions of competence for PA (e.g., extrinsic rewards, criticism, negative feedback)
Relatedness	Express a personal interest in the individual and take time to develop a rapport (MI)	PA counsellor listens to participants and shows personal involvement
	Prompt identification and seek available social support (MBCT)	PA counsellor prompts identification of sources of support for PA behavior change (if relevant), acknowledges challenges in recruiting adequate support (autonomous vs controlled), and promotes effective ways of seeking positive support
	Acknowledge and respect perspectives and feelings (MBCT)	PA counsellor makes statements of empathy, acknowledges participants’ perspectives, conflicts/ambivalence, distress, and negative affect, and expresses positive feelings when communicating with participants
	Provide support and encouragement (MI)	PA counsellor provides general support and encouragement
	Involvement (MI)	PA counsellor expresses a personal interest in participants and takes time to develop a rapport
	Encourage asking questions (MBCT)	PA counsellor prompts participants to pose questions regarding their PA goal progress and behavior
	Show unconditional regard (MBCT)	PA counsellor expresses positive support regardless of participants’ successes or failures
	Demonstrate/show interest in the person (MBCT)	PA counsellor provides statements of interest and curiosity about participants’ thoughts and perceptions, personal history and background, social context, life events, etc. when communicating with them
	Use empathetic listening (MBCT)	PA counsellor demonstrates attentiveness to participants’ responses (e.g., stays silent to allow participants to complete sentences), and provides reflective and summary statements when appropriate (directed at affect or content) when communicating with them. PA counsellor also asks participants for permission to provide new information, guidance, or advice

*Notes*. As previously mentioned, techniques may support more than one need, and it is implied that techniques used to foster needs satisfaction will also help to foster autonomous motivation [22]. MI = motivational interviewing. MBCT = motivation and behavior change techniques. PA = physical activity.

*Training and ongoing supervision of PA counsellors*. Owing to the nature of the intervention, PA counsellors who are current or past graduate students in kinesiology or a related field are hired. PA counsellors are trained, supervised, and supported by the first author (who holds a PhD in PA and health psychology) and the second author (who holds a masters in Human Kinetics). PA counsellors complete a 2–hour training session (conducted by the first and second authors), are observed performing a mock counselling encounter, and take part in a bracketing interview to examine how their own backgrounds, perceptions, and interests could impact them in their role. Ongoing supervision consists of 30–minute team meetings every 2 weeks focused on updates on participants’ progress, discussion of challenging sessions, deviations or modifications to sessions, and feedback on session notes. During these meetings, PA counsellors are invited to reflect on and discuss their experiences conducting the sessions. Of note, these meetings also serve to monitor data on outcomes, accrual, and adverse events, and oversee participants’ safety as a data monitoring committee is not needed for the ACCESS trial because the intervention is non-invasive with minimal risk of harm.

#### Usual care group

Usual care as a comparison group is necessary as the aim of a future large, full-scale RCT will be to compare the ACCESS intervention with *de facto* usual care (or treatment as usual). Without it, it would not be possible to claim that the ACCESS intervention be the new standard of care. Participants randomized to the usual care group are asked to continue their usual activities of daily living. No restrictions are placed on their PA behavior. Once participants complete follow-up assessments, study staff email them a copy of the intervention materials to review on their own in hopes that it could possibly lead to increases in PA even though they do not have an opportunity to engage with a PA counsellor. Another reason to provide participants randomized to the usual care group with a copy of the intervention materials once they complete follow-up assessments is to promote retention.

### Measures

#### Pilot RCT primary outcomes

*Feasibility [throughout the trial]*. Drawing on the CONSORT 2010 statement for pilot and feasibility trials [42] and CONSORT flow diagram, the following feasibility aspects are tracked by study staff: (1) number of months needed to reach target sample size; (2) number of young adults assessed for eligibility (with referral source) and reasons for exclusion (i.e., not meeting inclusion criteria, declined to participate, other reasons); (3) number of young adults who consented and reasons for refusal; (4) number of participants randomized and reasons for refusal; (5) number of participants allocated to the intervention group and the usual care group; (6) number of intervention sessions attended and proportion of participants who adhered to the intervention (i.e., attended all sessions); (7) number of participants who discontinued the intervention and reasons; (8) number and type of adverse events related to the intervention and/or trial procedures; (9) number of participants lost to follow-up (i.e., who do not complete post-intervention and follow-up assessments) and reasons; (10) number of participants analyzed, number excluded from analysis, and reasons; and (11) percentage of missing data on quantitative measures and number of participants who completed an interview. Study staff conduct a biweekly audit of these metrics (along with adverse events, if any); the first author/principal investigator reviews these during biweekly meetings.

Criteria were set a priori based on relevant literature and the authors’ experiences to determine feasibility of the intervention and trial protocol. The intervention and trial protocol will be considered feasible if: (1) target sample size is reached within 20 months; (2) 2–3 young adults are referred or self-refer per month and are assessed for eligibility; (3) ≥70% of eligible young adults consent and are randomized, with 50% being allocated to the intervention group and 50% to the usual care group, and ≤10% discontinuing the intervention; (4) ≥75% of participants in the intervention group complete all six videoconference sessions for an average of ≥50 minutes; (5) ≤25% of participants are lost to follow-up (i.e., ≥75% complete post-intervention and follow-up assessments) allowing for ≥22 participants (≥11 per group) to be analyzed; (6) <10% missing data on quantitative measures and ≥75% of participants are interviewed; and (7) no adverse events related to the intervention are reported. These data will serve to determine if/what changes/modifications are needed to improve the intervention and/or trial protocol, and will inform the timeline and budget for a large, full-scale RCT.

*Acceptability–participants [post-intervention period]*. All participants are invited to take part in an audio-recorded, semi-structured interview by phone or videoconferencing technology to share their opinions about the trial protocol. Additionally, participants in the intervention group are asked questions related to the intervention (i.e., content, delivery mode, length, duration, PA counsellor), SDT constructs, and BCTs/MBCTs. Their feedback will serve to determine if/what changes/modifications are needed to improve the intervention and/or trial protocol. It will also offer insight into the impact of the various intervention components in achieving the overall outcome of increased PA.

*Acceptability–PA counsellors [at trial cessation or contract termination]*. Each PA counsellor will be invited to take part in an audio-recorded, semi-structured interview by phone or videoconferencing technology to explore their experiences delivering the ACCESS intervention, as well as their thoughts about the content of the intervention, required training, ongoing supervision, using an intervention manual, conducting sessions using videoconferencing technology, maintaining fidelity to the manual, and their motivation and confidence to conduct the sessions. Their feedback will serve to determine if/what changes/modifications are needed to improve the ACCESS intervention and help to highlight factors that may facilitate or hinder the effectiveness of the intervention and/or its implementation in the future.

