### Trial design

The ACCESS trial is a parallel, two-arm pilot RCT with 1:1 allocation ratio, wherein quantitative and qualitative data are collected from the target population (i.e., young adults who have completed treatment for cancer; participants) and those delivering the intervention (i.e., PA counsellors). After providing informed consent digitally through a web-based form and completing baseline assessments of primary (i.e., PA behavior) and secondary (i.e., patient reported outcomes) effectiveness outcomes, young adults are randomized to one of two groups: (1) intervention group in which they receive a 12-week behavior change intervention delivered in real-time via videoconferencing technology; or (2) usual care (i.e., no intervention). Additional assessments are performed after the 12-week intervention period and at follow-up (i.e., 24 weeks post-baseline). Fig 1 summarizes the ACCESS trial design and the process of enrollment, randomization, assessments, and data analysis.

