### Randomization

Randomization is stratified by biological sex (male or female) to reduce a potential imbalance between groups. After baseline assessments are completed, participants are randomized to the intervention group or usual care group in a 1:1 ratio using the Clinical Trial Randomization Tool offered by the National Cancer Institute (https://ctrandomization.cancer.gov/) by a member of the first authors’ laboratory who is not involved in the who reveals group allocation to study staff, who then reveals group allocation to participants (after they completed their baseline assessments). This approach prevents study staff from knowing the sequence for new recruits or from influencing the sequence. In addition, since multiple participants can complete baseline assessments simultaneously, it is not possible for study staff to know what group participants will be assigned to until after baseline assessments are completed.

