*Adverse events [throughout the trial]*. Becoming more physically active is very safe for most young adults after cancer treatment ends and can yield many health benefits [71, 72]. Though the risk of injury is estimated to be very low in this trial, PA counsellors educate participants on the warning signs that may indicate a problem as per Canadian Society for Exercise Physiology guidelines (e.g., chest discomfort, unusual shortness of breath, dizziness or light-headedness, heart rhythm abnormalities) and tell participants to seek immediate medical attention should one of these signs occur. Adverse events (i.e., any unfavourable and unintended sign, symptoms, or disease) definitely, probably, or possibly related to engaging in PA or trial procedures (e.g., wearing an accelerometers) will be tracked. To this end, all adverse events occurring during trial participation are documented by PA counsellors. Each session, PA counsellors record any adverse event(s) participants share (if any) in their notes and report them immediately to the principal investigator via email. At the time of reporting, the intervention is paused for the participant reporting the adverse event until clearance from an appropriate healthcare provider to resume the intervention is obtained. All adverse events reported will be shared with Institutional Review Boards and reported in forthcoming publication of trial results. Additionally, there is a risk that participants experience distress in response to certain questions included in the questionnaire packages and/or posed during the interviews; participants receive a list of free resources to consult in case this occurs during the consent process (e.g., Canadian Cancer Society–Peer support / cancer information specialist: [name]).

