### Data management and analysis

#### Main analyses

Quality checks and content validation will be utilized to ensure high quality data (i.e., identify sources of inconsistency, checking for errors). Quantitative and qualitative data analyses will be conducted. SPSS and SAS will be used for quantitative data management and analysis; NVivo will be used for qualitative data management and analysis. Descriptive statistics will be computed to describe the sample based on baseline personal and medical factors, and report on feasibility and acceptability outcomes described above. Specifically, categorical variables will be described using proportions and frequencies, and continuous variables with means and standard deviations (or with medians and interquartile ranges for data not normally distributed). Content analysis [74] of the transcribed interviews will be conducted to identify themes and see if/what changes to the intervention and/or trial protocol are warranted.

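### The all-must-hold feasibility rule includes a zero-event criterion with no narrower event class and a 50/50 allocation clause, so one minor related event could label an otherwise feasible trial not feasible

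*Protocol article*

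**What the plan says.** Under Measures, Pilot RCT primary outcomes, the protocol article sets one rule: "The intervention and trial protocol will be considered feasible if: (1) target sample size is reached within 20 months". Six more numbered criteria follow, linked to the first by a plain conjunction:

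- (2) a monthly referral count;
- (3) at least 70% of eligible people consenting and randomised, "with 50% being allocated to the intervention group and 50% to the usual care group", and at most 10% discontinuing;
- (4) at least 75% of the intervention group attending all six sessions, with a minimum average length;
- (5) at most 25% lost, leaving at least 22 to analyse (11 per group);
- (6) under 10% missing data and at least 75% interviewed;
- (7) "no adverse events related to the intervention are reported".

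No tolerance, intermediate grade or partial pass is stated. The next sentence says that the data will be used to decide what to change and to plan the full-scale trial.

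The adverse events paragraph under Additional measures says what is tracked: "Adverse events (i.e., any unfavourable and unintended sign, symptoms, or disease) definitely, probably, or possibly related to engaging in PA or trial procedures". It adds "Though the risk of injury is estimated to be very low in this trial", without a figure. Trial design describes a "parallel, two-arm pilot RCT with 1:1 allocation ratio".

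**The concern.** Feasibility is a primary outcome of this pilot, and the rule for it is binary. Two of its parts do not measure feasibility well.

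**Criterion 7.** It tolerates no related event. The only definition in the article takes in any unfavourable sign or symptom, and criterion 7 is not tied to a narrower class. For any non-zero event risk, the chance of passing falls as more people are treated and as events are recorded more carefully. That is the wrong direction for a feasibility criterion.

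**The 50/50 clause.** The split is produced by the randomisation list. It says nothing about whether people can be recruited, retained or treated as planned.

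At stake is the pilot's main conclusion, which could come out as not feasible for reasons that have little to do with feasibility.

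**Working it through.** **The plan's own figure.** Criterion 5 gives at least 22 analysed, 11 per group. 30 × 0.75 = 22.5 and 15 × 0.75 = 11.25, so the figures reproduce when rounded down. Since 22/30 = 73.3%, the 75% cut-off in whole people is 23 of 30. The calculations below use 23.

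**Inputs from the protocol.** 30–40 randomised, 15–20 per group (Sample size), and the thresholds listed above.

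**Assumed inputs.** The risk that an intervention participant has at least one related event is not given, so it is varied from 1% to 10%. The number of eligible people is not given and is taken as N/0.7, that is 43 or 57. True rates are also assumed, in two scenarios.

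**Step 1: criterion 7 alone.** P(no event) = (1 − p)^n.

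| p | n = 15 | n = 20 |
|---|---|---|
| 1% | 86% | 82% |
| 2% | 74% | 67% |
| 3% | 63% | 54% |
| 5% | 46% | 36% |
| 10% | 21% | 12% |

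The criterion fails more often than not once p exceeds 1 − 0.5^(1/n), which is 4.5% for n = 15 and 3.4% for n = 20.

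**Step 2: five proportion criteria.** These are exact binomial probabilities. The moderately better scenario has 80% consent, 5% discontinuation, and 85% for attendance, retention and interviews.

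| Criterion | Passes if (N=30 / N=40) | Probability |
|---|---|---|
| Consent | ≥31 of 43 / ≥40 of 57 | 0.927 / 0.974 |
| Discontinuation | ≤1 of 15 / ≤2 of 20 | 0.829 / 0.925 |
| Attendance | ≥12 of 15 / ≥15 of 20 | 0.823 / 0.933 |
| Retention | ≥23 of 30 / ≥30 of 40 | 0.930 / 0.970 |
| Interviews | ≥23 of 30 / ≥30 of 40 | 0.930 / 0.970 |

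The product under independence is 0.547 (N=30) and 0.790 (N=40). In the clearly better scenario (85% consent, 3% discontinuation, 90% for the other three) it is 0.855 and 0.964.

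**Step 3: add criterion 7.** Multiply by the Step 1 probability.

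| Scenario | 1% | 2% | 5% |
|---|---|---|---|
| Moderately better, N=30 / 40 | 0.47 / 0.65 | 0.40 / 0.53 | 0.25 / 0.28 |
| Clearly better, N=30 / 40 | 0.74 / 0.79 | 0.63 / 0.64 | 0.40 / 0.35 |

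**Step 4: dependence among the criteria.** The criteria overlap: someone who discontinues cannot attend all six sessions. Independence therefore understates the joint chance. The joint chance of the five cannot exceed the smallest component, 0.823 or 0.925 in the moderately better scenario. Multiplying by Step 1 gives ceilings of 0.61 / 0.62 at 2% risk and 0.38 / 0.33 at 5%. So at 5% the rule fails more often than not however the five criteria are correlated, whereas at 2% it may pass more often than not.

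Recruitment time, referral rate, session length and missing data are not modelled. If any of them can fail, the joint chances are lower.

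**Step 5: the 50/50 clause.** Read as the planned 1:1 ratio, it is met by design and tests nothing. Read literally, it cannot hold at an odd total. At an even total under simple randomisation its probability is C(N, N/2)/2^N, which is 0.14 for N=30 and 0.13 for N=40. With assumed permuted blocks of 2 to 6 in two sex strata (75% female assumed), simulation gives about 0.51 to 0.75, with arm sizes within one person of N/2 in at least 96% of runs. The joint figures in Step 3 leave this clause out.

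**The case against.** The strongest reply is that the rule is not used as a gate. The protocol's next sentence puts the results to work on modifications, timeline and budget, and no stop decision is attached. That softens the consequence. It does not remove the rule, which still states when the trial counts as feasible, and it sits awkwardly with an all-or-nothing verdict.

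A reader might infer that a truly feasible trial would most likely be declared not feasible. The documents do not support this. It needs an event rate that they do not give, and with clearly better true rates and 1–2% risk the modelled criteria pass with probability 63–79%. The protocol does call the risk of injury very low, although injury is narrower than any unfavourable sign or symptom.

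A reader might also take it as settled that a merely possibly related event fails criterion 7. That wording governs what is tracked, and it covers trial procedures as well, whereas criterion 7 speaks of the intervention. The defect is that the link between the two is left open.

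Nor does the text require an exact 50/50 split; the nominal 1:1 reading is the natural one. The 37 randomised under Trial status is an interim count and shows only that odd totals occur.

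Finally, it would be wrong to say that every cut-off rests on 15–20 people. Only discontinuation and attendance do. Retention and interviews use all 30–40 participants, and consent uses everyone eligible. Main analyses says that "categorical variables will be described using proportions and frequencies", but intervals may be specified in an analysis plan not shown here, so their absence is not counted against the protocol.

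**Conclusion.** The point holds as a defect in how the feasibility rule is fixed. Seven criteria must all be met, one of them tolerates no related event without saying which class of event counts, and another contains a clause that does not measure feasibility.

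The size depends on a risk that the protocol does not state. The zero-event criterion alone costs 14–18 percentage points at 1% risk, 26–33 at 2% and 54–64 at 5% (100% minus the Step 1 values). With moderately better true rates it brings the joint pass chance from 55–79% down to 40–53% at 2% or 25–28% at 5%, assuming independence, which understates these chances. With clearly better rates and low risk the trial would more likely pass than fail. The supportable conclusion is that the trial could be labelled not feasible because of a single minor event, not that it probably will be. The change is worth making because it is cheap and concerns a primary outcome.

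**What to change.** 1. Remove the 50/50 clause from the feasibility criteria. The numbers allocated to each group are already among the tracked metrics.
2. Restrict criterion 7 to a class of related events that the investigators state in advance, for example serious ones, and state which degrees of relatedness count. Keep reporting all related events as a count and a rate with an exact confidence interval.
3. Classify each criterion separately as met, met with modification, or not met. This matches the stated purpose of deciding what needs changing.

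As a secondary suggestion, give the other feasibility proportions exact 95% intervals if the analysis plan does not already do so. Attendance of 15 of 20, for instance, meets the 75% criterion with an interval of 51–91%.

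The cost is a rewording and a few intervals, with no change to trial conduct. The downside is that the verdict becomes graded rather than yes or no. Because recruitment was well advanced when the article was written, the change should be dated and described as a clarification of the criteria.
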